## 2. Methods and Design

### 2.1. Objectives

This study aims to (1) re-evaluate the efficacy of acupuncture and flunarizine on migraine treatment; (2) compare the similarities and differences in brain activity and gut microbiota associated with acupuncture and flunarizine treatment for migraine; and (3) investigate the correlation between symptom improvement, brain activity changes, and gut microbiota regulation elicited by acupuncture and flunarizine.

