#### 2.9.4. Tripartite Network Analysis

A tripartite network analysis based on graph theory will be used to compare the interactions among brain network activity, gut microbiota, and clinical data for migraineurs in the acupuncture and flunarizine groups. The interactions between the phenome (clinical symptoms), gut microbiome (fecal microbial community), and connectome (indices of regional centrality in the brain) will be analyzed using Spearman's correlations in MATLAB R2015b. Fisher's *r*-to-*z* transformation will be used to measure the correlation coefficient difference between the acupuncture and flunarizine group. The *Z* test will be applied, and an uncorrected value of *p* < 0.05 will be considered statistically significant. The software Cytoscape 3.7.2 (https://cytoscape.org) will be used to visualize and generate a brain activity, gut microbiota community, and clinical data interaction network. This association of this network will be included if Pearson's correlation for the data of the different groups achieves significance. The architecture of different group networks will be based on a significantly different network. The results will be described in terms of direct (correlations with microbial community) and indirect effects (clinical symptoms and brain connectivity metric) with an emphasis on the interaction between microbiome and clinical symptoms. An independent sample *t*-test will be used to examine between-group differences in clinical variables.

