Currently, positive control is one of the most commonly used control methods in randomized controlled trials (RCTs). The calcium channel blocker flunarizine, recognized as a first-line treatment for migraine [22–25], is widely used as a comparator in RCTs [37, 75, 76]. This control design is a good way to compare the efficacy, tolerability, and safety of different medical interventions for migraine. The present study is the first one to investigate the brain-gut regulatory mechanisms underlying different interventions (acupuncture versus flunarizine) for migraine.

Therefore, taking the brain-gut regulatory mechanisms as a starting point for this study, we will combine brain neuroimaging and gut microbiological data to analyze the similarities and differences of acupuncture and flunarizine treatment for migraine. This will permit investigation of the correlations between clinical efficacy and changes in gut microbiota and brain network function elicited by acupuncture and flunarizine treatment based on tripartite network analysis. It is hoped that the findings will inform efforts to partially reveal the common and different mechanisms of acupuncture and flunarizine on the treatment of migraine.

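### Section 2.9.4 gives two network rules that pull apart; read literally, the second drops links shared by both arms, so the networks cannot show common mechanisms

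*Protocol article*

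**What the plan says.** Section 2.9.4 (Tripartite Network Analysis) sets out these steps in order.

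- The analysis "will be used to compare the interactions among brain network activity, gut microbiota, and clinical data for migraineurs in the acupuncture and flunarizine groups".
- Interactions between symptoms, microbiome and regional brain centrality "will be analyzed using Spearman's correlations in MATLAB R2015b". No between-arm condition applies at this step.
- Fisher's r-to-z "transformation will be used to measure the correlation coefficient difference between the acupuncture and flunarizine group". A Z test follows, in which an uncorrected p below 0.05 "will be considered statistically significant".
- After naming the software that draws the network, the section gives an inclusion rule: "This association of this network will be included if Pearson's correlation for the data of the different groups achieves significance".
- The next sentence gives a second rule: "The architecture of different group networks will be based on a significantly different network".

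Two other places say what the analysis is for. Objective 3 in section 2.1 is to "investigate the correlation between symptom improvement, brain activity changes, and gut microbiota regulation elicited by acupuncture and flunarizine". The Discussion names the tripartite analysis as the route to the correlations under both treatments, and hopes that the findings will help to "partially reveal the common and different mechanisms of acupuncture and flunarizine on the treatment of migraine". Section 2.9.4 states no rule for identifying a link that is common to both arms.

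**The concern.** The two rules answer different questions. The first asks whether an association exists (null: the correlation is zero). The second, if it refers to the Z test, asks whether the arms differ (null: the two correlations are equal). A strong link of the same size in both arms satisfies the second null, so a filter on that test discards it however strong it is. Such a link is what a common mechanism would look like.

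At stake is how the networks are read. If edges are selected because the arms differ, the picture will suggest that the treatments work through different pathways, whatever the truth. The few shared links that pass do so because sampling error pushed the two estimates apart, and many of those would look specific to one treatment.

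This is separate from the lack of multiplicity correction. A stricter threshold for the Z test would remove shared links even more completely.

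**Working it through.** **Inputs.** From the protocol article: 30 patients per group required and 66 recruited, so 33 per group (section 2.5.1); Spearman correlations, a Pearson screen, and Fisher r-to-z with a Z test at 0.05 (section 2.9.4). Assumed, because the article gives no correlations: bivariate normal data with the same true correlation rho in both arms, from 0.2 to 0.6.

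**The plan's own figure.** Section 2.9.4 has no computed figure. The sample size that supplies n reproduces. The pooled SD is √((3.5² + 2.3²)/2) = 2.96, the difference is 4.1 − 1.9 = 2.2, and the exact two-sample t-test has power 0.794 at 29 and 0.808 at 30 per group. Then 30 × 1.1 = 33 per group, or 66.

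**Step 1: what the difference filter demands.** Z = (z₁ − z₂)/√(2/(n − 3)), with z = artanh(r).

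- n = 30: SE = √(2/27) = 0.272 and 1.96 × 0.272 = 0.533. If one arm's observed correlation is 0, the other must reach tanh(0.533) = 0.49.
- n = 33: SE = √(2/30) = 0.258, threshold 0.506, so 0.47.
- Significance within a single arm needs only about 0.36 (n = 30) or 0.34 (n = 33).

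**Step 2: a link equal in both arms.** With equal true correlations Z has mean zero whatever rho is, so P(|Z| > 1.96) is about 0.05. Spearman's z has a somewhat larger variance; taking it as 1.06/(n − 3) gives P(|Z| > 1.96/√1.06) = P(|Z| > 1.90) ≈ 0.057.

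**Step 3: simulation, n = 30 per arm, 20,000 trials per setting.** Kept means that the Z test is significant and Pearson is significant in at least one arm.

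| True rho, both arms | Kept under the difference rule | Pearson significant in both arms | Gap (points) |
|---|---|---|---|
| 0.2 | about 4% | about 4% | none |
| 0.3 | about 5% | 14% | 14 − 5 = 9 |
| 0.5 | about 6% | 68% | 68 − 6 = 62 |
| 0.6 | about 6% | 91% | 91 − 6 = 85 |

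With Spearman in place of Pearson, both-arm significance is 11%, 60% and 85% at rho 0.3, 0.5 and 0.6 with n = 30, and 13%, 66% and 89% with n = 33. The kept rate stays within 4-6% at n = 33.

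**Step 4: what the survivors look like.** At rho 0.5 and n = 30, about 71% of the shared links that pass the filter are significant in only one arm. They would be drawn as treatment-specific although the true correlations are equal.

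**Step 5: what could identify a shared link.**

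- A non-significant Z test cannot. With true correlations of 0.6 and 0 and n = 30, its power is about 67% by simulation and 72% by formula (artanh(0.6)/0.272 = 0.693/0.272 = 2.55; Φ(2.55 − 1.96) ≈ 0.72). It misses roughly three in ten real differences of that size.
- A significant average of the two arms' Fisher z values cannot either. At n = 30 it is significant 68% of the time with true correlations of 0.6 and 0, and 85% with 0.7 and 0, where no link is shared.

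**The case against.** The strongest reply is that the text is unclear and that only one reading does the damage. Nothing joins the two rules, and the first, taken alone, would keep shared links. The section does not say that the significantly different network means edges that pass the Z test, and the sentence could describe a separate between-arm display. This stands in part. The Z test is the only test of difference that the section defines for correlations, so the literal reading is the natural one, but it is not the only one. If both rules apply, shared links go; if they are alternatives, the article does not say which governs. Either way the section needs rewording.

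A second reply is that a reader might infer that the correlations of objective 3 can no longer be found. The article does not support that. The Spearman correlations are computed before any between-arm test, and objective 3 asks to investigate correlations, not to test for shared ones. This reply stands in full: the loss is in the networks. Reading shared links off the unfiltered correlations would, however, follow no stated rule.

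Third, the section's declared aim is to compare the arms, which a difference test suits. The similarities in objective 2 concern brain activity and microbiota, which sections 2.9.2 and 2.9.3 address, and the Discussion's wording is only a hope. That is fair, but the Discussion ties the hope to this analysis.

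Fourth, the loss depends on the assumed correlation. This stands: at 0.2 there is none against both-arm significance, and at 0.3 about 9 points.

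**Conclusion.** The point holds as a conflict between two inclusion rules, one of which, read literally, works against the stated hope of finding common mechanisms. Under that rule a link equal in both arms stays in the networks about 4-6% of the time (30-33 per arm, assumed rho 0.2 to 0.6, bivariate normal data). The gap against both-arm significance at 30 per arm runs from nothing at rho 0.2 to about 85 points at rho 0.6.

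It does not follow that shared links are always removed, since a few survive by chance, or that the underlying correlations are lost. The analysis is exploratory; the primary outcome and the sample size are untouched. The change should be made because the rule as written tilts the network readout towards treatment-specific links, and rewording it is cheap.

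**What to change.** In section 2.9.4, replace the sentence on the architecture of the group networks and reconcile it with the Pearson inclusion sentence, as follows.

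1. Build each arm's network from within-arm correlations, with one coefficient throughout (the section now uses Spearman for the analysis and Pearson for inclusion) and no between-arm filter.
2. Report the Fisher Z comparison as a separate layer that marks the edges that differ between arms.
3. Call a link shared only if it is significant in both arms with the same sign, and report it with a confidence interval for the difference in correlation. State that a non-significant Z test alone is not evidence of a common link.
4. Optionally report a pooled within-arm Fisher z with its confidence interval as an overall estimate of association, not as the test for a common link.

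The cost is a change of wording and a little more analysis of data already planned. The drawbacks are larger networks to display and one more family of exploratory tests. At 30-33 per arm the shared-link criterion will itself find few links with correlations near 0.3 or below, and the report should say so.

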### 2.5. Sample Size, Randomization, and Blinding

#### 2.5.1. Sample Size Calculation

Following a previous study, we anticipate that the change in the average number of migraine days in the acupuncture group will be 4.1 ± 3.5, and in the flunarizine group, it will be 1.9 ± 2.3 [37]. Assuming that *α* = 0.05 and 1 − *β* = 0.80, 30 patients will be required for each group, as calculated using *G*^*∗*^Power V3.1.9.2 software. There is no consensus on sample size for neuroimaging and gut microbiota research. A review of previous similar studies suggests that 12–27 individuals in each group is a reasonable sample size for stable and reliable results [49, 50]. Finally, a total of 66 patients will be recruited to compensate for a withdrawal rate of 10%.

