### 2.9. Statistical Analysis

#### 2.9.1. Clinical Data Analysis

The analysis plan will be determined before the study is conducted. Demographic characteristics, baseline characteristics, and clinical outcomes will be analyzed using SPSS25.0 statistical software based on the intention-to-treat population, which comprises subjects who receive, at least, one treatment and undergo, at least, one posttreatment efficacy evaluation. Missing data will be replaced by data from the last observation. Normally distributed continuous variables will be presented by means and standard deviations with 95% confidence intervals. Nonnormally distributed continuous variables will be described using medians and interquartile ranges. Categorical variables will be described using percentages and frequencies. The significance level used for statistical analysis with 2-tailed testing will be 5%. Qualitative data will be compared using the chi-square test. If the quantitative data are normally distributed, we will use analysis of variance to detect differences between the two groups; if not, the Mann–Whitney test will be used. Data sheets will be anonymized for data entry, and statistical analysis will be conducted by an independent statistician blinded to treatment allocation.

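### Section 2.9.4 reports pairwise correlations as direct and indirect effects, although no test it names can tell the two apart

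*Protocol article*

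**What the plan says.** Section 2.9.4 (Tripartite Network Analysis) sets up three layers: "The interactions between the phenome (clinical symptoms), gut microbiome (fecal microbial community), and connectome (indices of regional centrality in the brain"). Associations between the layers "will be analyzed using Spearman's correlations in MATLAB R2015b". The arms are compared by Fisher's r-to-z transformation and a Z test, for which "an uncorrected value of *p* < 0.05 will be considered statistically significant". For the drawn network the section adds: "This association of this network will be included if Pearson's correlation for the data of the different groups achieves significance".

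It then fixes how the results will be worded: as "direct (correlations with microbial community) and indirect effects (clinical symptoms and brain connectivity metric"), with the emphasis on the microbiome and clinical symptoms.

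The section names no partial correlation, conditional network, path model or mediation test. Nothing in it requires a link called indirect to pass through a microbial variable. The aim that the network serves, objective 3 in section 2.1, is to investigate correlation between symptom improvement, brain changes and microbiota changes.

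**The concern.** A pairwise correlation tests whether two variables are associated, with everything else ignored. A direct effect of a microbe on a symptom is a different hypothesis: that an association remains once the brain metric is taken into account. An indirect effect is different again: that a path runs from microbe through brain to symptom. The section uses the vocabulary of the second and third hypotheses and the test of the first.

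Two consequences follow from the wording alone. A microbe-symptom correlation counts as direct even if the brain carries all of it. A brain-symptom correlation counts as indirect although its test contains no microbial variable, so the result is the same whether or not microbes play any part.

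What is at stake is the mechanistic conclusion. The Discussion presents the trial as a study of brain-gut regulatory mechanisms, and readers of the results are likely to take direct and indirect literally. This is not a detail left to an unseen analysis plan, because the article itself states the labels and the rule that assigns them.

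**Working it through.** **Inputs from the document**
- Patients per arm. Section 2.5.1 assumes that the change in migraine days "in the acupuncture group will be 4.1 ± 3.5, and in the flunarizine group, it will be 1.9 ± 2.3", with α = 0.05 and power 0.80, and concludes that "30 patients will be required for each group". This reproduces: the SD is √((3.5² + 2.3²)/2) = √8.77 = 2.961, the difference is 4.1 − 1.9 = 2.2, and d = 2.2/2.961 = 0.743. A two-sided t test then needs 30 per arm (power 0.808). Adding 10% to 60 gives 66, or 33 per arm.
- Test. Spearman correlation, two-sided 5%. Section 2.9.4 gives 0.05 for the Z test; its use for single correlations is an assumption here, as is two-sidedness, which section 2.9.1 states for the clinical data.

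**Assumed, because the document gives no figure**
- Path strengths. Model: microbe M → brain metric B → symptom S, with both path correlations equal to *a*, normal variables and no direct path. *a* is varied over a range.

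**Step 1: what the pairwise test sees.** In this chain the population correlation of M and S is a × a = a², although the direct effect is zero. The test statistic is t = r√((n − 2)/(1 − r²)). At n = 30 the critical value is t = 2.048 on 28 degrees of freedom, so a correlation is significant when |r| > 2.048/√(28 + 2.048²) = 0.361. At *a* = 0.6 the population value is 0.36, close to that threshold, so a rejection rate a little under one half is expected.

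**Step 2: simulation**, 20,000 data sets per setting, one arm, n = 30:

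| Path correlation *a* | Population M-S correlation a² | Pairwise test significant, so called direct |
|---|---|---|
| 0.2 | 0.04 | about 5% |
| 0.3 | 0.09 | 7% to 8% |
| 0.4 | 0.16 | about 13% |
| 0.5 | 0.25 | 24% to 25% |
| 0.6 | 0.36 | 46% |
| 0.7 | 0.49 | 75% |
| 0.8 | 0.64 | 96% |

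With 33 per arm, paths of 0.5, 0.6, 0.7 and 0.8 give 26%, 50%, 79% and 97%.

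**Step 3: the same chain, conditioning on the brain metric.** The partial correlation is (r_MS − r_MB·r_BS)/√((1 − r_MB²)(1 − r_BS²)). Its numerator is a² − a·a = 0, so the null holds. The partial Spearman test (n − 3 degrees of freedom) is significant in 5.2% to 6.7% of data sets for *a* from 0.5 to 0.8.

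**Step 4: the indirect label.** A brain-symptom correlation of 0.5 is significant in 77% of data sets at n = 30. M does not enter the calculation, so this is also the rate at which the indirect label is given when no microbe is involved.

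**Step 5: where conditioning fails.** Suppose instead that M and S each act on B and are otherwise unrelated. The pairwise M-S correlation is then 0, and the planned test rejects in 5%. The partial correlation given B is −a²/(1 − a²): −0.16/0.84 = −0.19 at *a* = 0.4, −0.25/0.75 = −0.33 at 0.5 and −0.36/0.64 = −0.56 at 0.6. The partial test falsely indicates a direct link in 14%, 33% and 80% of data sets.

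**The case against.** **The terms may be graph vocabulary.** The parentheses can be read as edge classes: edges that touch a microbial node, and edges that do not. On that reading nothing is put in the wrong class. The reading is possible, but the section says effects and does not define the words in this way. If edge classes were meant, the renaming below is exactly the correction needed.

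**The aims are associational.** Objective 3 speaks of correlation, and the Introduction and Discussion speak of exploring relationships. This is true, and no mediation estimate is promised. It means that the reporting rule in section 2.9.4 claims more than the objective asks.

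**The simulation covers only part of the rule.** It tests one correlation in one arm. The section also compares arms, and it is unclear whether only edges that differ between arms are kept. If so, a chain identical in both arms passes the Z test in only 5% to 6% of data sets for paths from 0.2 to 0.7. Edge inclusion also uses Pearson rather than the Spearman correlation simulated here. The percentages are therefore rates for a single-arm pairwise test, not rates at which the final network will report such an edge.

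**Partial correlation is not a clean cure.** This stands. The Discussion describes communication in both directions between gut and brain, so the situation in step 5 cannot be ruled out. Measurement error matters too: with an assumed reliability of 0.6 for the brain metric, the partial test in the chain model rejects in 16% (paths 0.6) and 31% (paths 0.7).

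**Conclusion.** The point holds as a mismatch between labels and tests. Section 2.9.4 commits the trial to statements about direct and indirect effects that none of its named tests can support. This follows from the text and needs no simulation.

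The size of the first mislabel is conditional. Under an assumed complete chain with equal paths and 30 per arm, it runs from the nominal 5% at paths of 0.2 to 75% at 0.7. The document cannot show that such chains exist or how strong they are.

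Three stronger conclusions might be inferred, and the document supports none of them:
- That the plan mislabels pathways at rates far above 5%. This is so only for moderate to strong paths; at weak ones the excess nearly vanishes.
- That the 77% in step 4 is a false-positive rate. It is the power to detect a real brain-symptom correlation of 0.5. The association is genuine, and only its name is unsupported.
- That partial correlations should replace pairwise ones as the rule for the labels. Step 5 shows that this can do worse than the planned test when the brain metric is a common consequence of microbe and symptom.

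The primary outcome, the sample size and the comparison of clinical efficacy are untouched. The harm is confined to the brain-gut interpretation.

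**What to change.** In section 2.9.4:

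1. Replace direct and indirect effects with *microbe-linked associations* (edges with a microbial variable at one end) and *brain-symptom associations* (edges without one).
2. Add a sentence that pairwise correlations do not separate a direct microbe-symptom link from one carried by the brain, and that the analysis serves the correlation objective in section 2.1.
3. Optionally, for any microbe-brain-symptom triple discussed as a pathway, report partial Spearman correlations as a sensitivity analysis: microbe-symptom given brain, and brain-symptom given microbe. State the assumptions for reading them: the brain metric lies between microbe and symptom, is measured without much error, and is not a common consequence of both. These results should not decide which edges are called direct or indirect.

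Steps 1 and 2 cost only wording. Step 3 needs a few lines of code on data already planned and loses one degree of freedom per test. The real price is a more modest mechanistic claim.

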## 3. Discussion

The pathogenesis of migraine is still controversial, the main reason of which is that multiple factors are involved, such as blood vessels, neurons, inflammatory mediators, abnormal brain structure and function, and genetic inheritance [53]. However, the recent research related to the regulation mechanism of brain-gut interaction seems to shed new light on the pathogenesis of migraine [17]. The brain-gut interaction is considered an important regulatory mechanism to integrate the brain with the gastrointestinal tract. Research on an integrative model for gut-brain interaction disorders has confirmed that the mediation in gut-to-brain communication and brain-to-gut communication is performed by different pathways [21]. However, information transmission between the gastrointestinal tract and the brain is mainly conducted via the nerve, endocrine, immunity, and gut microbiota pathways [54]. Gut microbiota is closely related to human health and disease through a long-term evolutionary selection process [55]. Gut microbiota and its metabolites are involved in the regulation of brain function and behavior [56, 57]. A lack or deficiency of gut microbiota can affect the normal development of the central nervous system [58], and such abnormality obviously exists in the gut microbiota structure of patients with central nervous system disorders [59–61].

Multiple factors are involved in the interrelationship of the brain and gut in migraine, such as neuropeptides, inflammatory mediators, gut microbiota, stress hormones, and nutritional substances [16]. A latest study has found the differences in composition and function of gut microbiota in the comparison of migraineurs and healthy control [15]. Moreover, previous fMRI studies have confirmed that abnormal architecture and connectivity in the brain network of migraineurs [62–64]. Recently, a human research has identified that the shifts of gut microbiota composition profile are correlated with the signal changes of brain activities involved in the cingulum and cerebellum [65].

Several studies linked to the effects of acupuncture on the structural characteristics of gut microbiota have shown that acupuncture stimulation can substantially improve the diversity of gut microbiota and the content of beneficial microflora [36, 66, 67]. Our previous studies have indicated that the analgesic effect of acupuncture may be related to the findings that acupuncture could regulate the functional connectivity of brain and the response of brain regions in the pain matrix in migraineurs [39, 68]. It seems to be a new direction and strategy to explore the brain-gut regulatory mechanisms of migraine treatment in the combination of neuroimaging and gut microbiological analysis. fMRI is a dynamic visualization technology to observe brain activities on the basis of different blood-oxygen state in various brain regions and is extensively applied in the acupuncture mechanism for pain diseases [69, 70]. The gut microbiological analysis is based on 16S rRNA high-throughput sequencing of fecal samples, which can amplify 16S rRNA fragments using a polymerase chain reaction to achieve taxonomic identification and accurate quantification of the gut microbiota community. At present, this technology has been widely used in the diagnosis and treatment of clinical diseases, such as cancer [71], diabetes [72], and Crohn's disease [73].

To shed light on the brain-gut regulatory mechanisms, the relationship among clinical efficacy, gut microbiota, and functional connectivity of the brain network should be investigated. Via assessing brain connectivity with the structural and functional network analysis, it can be quantified that the functional and anatomical integrity and information flow in the whole brain network [74]. Thus, we will use a tripartite network analysis based on graph theory to inquire and visualize the relationship between clinical efficacy with gut microbiota and brain network connectivity.

Currently, positive control is one of the most commonly used control methods in randomized controlled trials (RCTs). The calcium channel blocker flunarizine, recognized as a first-line treatment for migraine [22–25], is widely used as a comparator in RCTs [37, 75, 76]. This control design is a good way to compare the efficacy, tolerability, and safety of different medical interventions for migraine. The present study is the first one to investigate the brain-gut regulatory mechanisms underlying different interventions (acupuncture versus flunarizine) for migraine.

Therefore, taking the brain-gut regulatory mechanisms as a starting point for this study, we will combine brain neuroimaging and gut microbiological data to analyze the similarities and differences of acupuncture and flunarizine treatment for migraine. This will permit investigation of the correlations between clinical efficacy and changes in gut microbiota and brain network function elicited by acupuncture and flunarizine treatment based on tripartite network analysis. It is hoped that the findings will inform efforts to partially reveal the common and different mechanisms of acupuncture and flunarizine on the treatment of migraine.

